## Abstract

**Background:**

Physical training is recommended in various national and international guidelines for patients with cancer. Observational studies have shown that physical activity leads to reduced recurrence and mortality rates by 20–40% in colorectal, breast, and prostate cancer. Despite existing evidence, a systematic care structure is still lacking. The primary aim of this study is to implement and evaluate an online training platform to strengthen physical performance and patient empowerment after cancer surgery.

**Methods:**

The evaluation will be conducted as a prospective multicenter randomized controlled trial with three subgroups (colorectal-, breast-, and prostate cancer). Each group will include 100 patients (total 300 patients including dropouts; clinical stages T1–3 and/or N+; M0 after surgery intervention) and the primary endpoint (13% increase in the maximal oxygen consumption during exercise) will be examined. The intervention group will receive a 6-month home-based online training (2–3 times per week strength-endurance training using video presentations), bidirectional activity feedback information, online communication, and online counseling. The control group (usual care) will be advised lifestyle improvement. In-hospital testing will be performed before, during, and after the intervention. In addition to cardiopulmonary capacity, tumor specific diagnostics (liquid biopsy, depression and fatigue assessment, metabolic and endothelial screening) will be applied.

**Discussion:**

Due to the increasing incidence of cancer, associated with considerable mortality, morbidity and impaired quality of life, there is an imperative requirement for improved cancer care, of which structured physical training may become an integral component.

**Trial registration:**

DRKS-ID: DRKS00020499; Registered 17 March 2020.

## Background

Prostate cancer and breast cancer are the most common malignant tumors in men and women, respectively with approximately 60,000–70,000 new cases each per year in Germany. Colorectal carcinoma affects women and men with an increasing incidence of approximately 60,000 new cases per year [1]. The etiology of these malignancies is multifactorial. It includes genetic, environmental, and lifestyle factors such as nutrition, alcohol consumption, and smoking. Physical inactivity can increase cancer mortality [2]. Therefore, regular exercise is one of the most effective cancer prevention mechanisms [3–5]. Exercise also has a positive effect on the prevention of cancer recurrence. Regular training has been shown to result in a reduction of approximately 20–40% in the risk for colorectal, breast, and prostate cancer [6–12]. A strong positive correlation has been demonstrated between weekly energy consumption [10] and cardiorespiratory fitness [13] and tumor-related mortality rate [14]. In addition, regular training has been shown to improve cancer-related symptoms such as fatigue, muscle loss, metabolic syndrome and diabetes, and chronic cardiovascular inflammation. The benefits of regular training are also applicable to comorbidities such as anxiety disorders, depression [15], cognitive deficits, and dementia [16], which can further impair quality of life and therapeutic adherence of patients [17].

The World Health Organization, the European Society for Medical Oncology and the American Cancer Society recommend at least 150 min of moderate exercise or 75 min of vigorous exercise per week for all adults for primary and tertiary cancer prevention.

However, in patients undergoing chemotherapy, chemoradiotherapy, or cancer surgery, these recommendations are often not fully applicable and must be adapted to the patients’ individual level of performance. Consequently, training mode, training frequency, and intensity must be individually set according to personal performance and adapted according to the postsurgical conditions. Further individual adaptions are also necessary in the course of the therapy [18]. Essential factors to maintain the patients’ adherence to the training program include ongoing personal support, consideration of patients’ individual capability with thorough online training adjustment, and a bidirectional communication with the counseling team.

Training-associated decrease in cancer-related mortality rates is multifactorial. Several pathways and mechanisms have been discussed previously, which include regulation of tumor growth via phosphoinositide 3-kinase pathway [19], microRNA regulation [19, 20], decrease in circulating tumor cells [21], more consistent application of chemotherapy [22], attenuated epithelial-mesenchymal transition and tumor cell migration [23], and altered DNA methylation [24].

The available literature is primarily based on questionnaire surveys, instructions for lifestyle changes, and qualitative implementation of the training programs with subjective assessment of the intensity [25]. Despite the strong evidence and the preventive and regenerative efficiency of physical training, systematic implementation or adequate care structure are lacking in cancer therapy.

The **C**olo**R**ectal, **B**reast, and **P**rostate Cancer - **T**elemonitoring and **S**elf-management project (CRBP-TS) addresses these issues. The study aims to combine online-supported training, automated recording of activity and performance parameters, cross-sectoral bidirectional data evaluation, and online communication based on an electronic case file, which is accessible to patients as well as physicians. The objective of this study is to implement and evaluate an online training platform to strengthen physical performance and patient empowerment after cancer surgery. The primary outcome is 13% increase in maximal oxygen consumption during exercise (VO_2_ max) in the intervention group (IG) when compared with the control group (CG) after training for 6 months.

## Methods

### Study design and ethical approval

This prospective multicenter randomized controlled trial is organized by the Institute of Sport Medicine and Prevention, University of Leipzig, Germany and the Department of Visceral, Transplant, Thoracic, and Vascular Surgery, University Hospital of Leipzig, Germany. The study is approved by the Ethical Committee of the Medical Faculty, University of Leipzig (reference number 056/20-ek) and will be conducted in accordance with the principles in the latest revision of the Declaration of Helsinki. Any modifications to the study protocol will require a formal amendment to the protocol. The study has undergone external peer-review by the funding body and is funded by the State Ministry for Higher Education, Research and the Arts, Free State of Saxony, Germany.

### Study group, screening, and recruitment

The patients will be screened, informed, and included in the study at three University Hospitals in Germany (Dresden, Leipzig, and Hannover Medical School). Written informed consent will be obtained from all participants. The target groups of the study are cancer patients with International Classification of Diseases codes C18/19/20 (colorectal cancer), C50 (breast cancer), and C61 (prostate cancer) who underwent curative (R0) surgery at stages T1N0M0 to T3N3M0. Inclusion and exclusion criteria are presented in Tables 1 and 2. The patients will be informed and educated postoperatively before discharge from the hospital about program content and aims, randomization, and the consequences for the control group by the study team or the clinic stuff. Individuals interested in participating will then provide written informed consent after a sufficient period for reflection and further verbal discussion with an investigator. Participant insurance was contracted for study-related harm to study participants.

**Table 1 Tab1:** Inclusion criteria

#	Inclusion criteria
1	Resected colorectal carcinoma (C18/C19/C20) or breast carcinoma (C50) or prostate carcinoma (C61) up to 6 months after surgery, clinical stages T1–3 and/or N+; M0 according to UICC 8th edition; completed neoadjuvant chemotherapy, and achieved R0 resection
2	Female or Male
3	Age between 18 and 75 years
4	ECOG (Eastern Co-operative Oncology Group) < 1 without acute cardiac, renal, hepatic, endocrine, bone marrow or cerebral disorder
5	Cognitive ability of the patient to understand the postoperative program and to participate actively [26, 27]

**Table 2 Tab2:** Exclusion criteria

#	Exclusion criteria
1	Complication after tumor resection, which prolong convalescence and may impair adherence to the study interventions
2	Presence of a second malignant tumor (unless curatively treated > 5 years ago)
3	Orthopedic, rheumatological, cardiovascular or neurological (epilepsy, stroke, Parkinson’s disease, muscle wasting diseases such as amyotrophic lateral sclerosis, atrophy, cachexia or multiple sclerosis) contraindications for the exercise program
4	Inability to use the internet or the required applications (tablet, activity tracker, CRPB-TS App)
5	Each active disease, which affects adherence to the study procedures
6	Active alcoholism or illegal drugs consumption within the last six months before study entry
7	Missing patients’ compliance or inability to communicate in German

### Randomization

Patients will be randomly assigned to the intervention group (IG) or the control group (CG) following a 1:1 allocation by the Clinical Trial Centre, Leipzig. Randomization will be stratified by using a dynamic minimization algorithm with two factors: the cancer entity (colorectal, breast, or prostate carcinoma) and the gender (only by colorectal carcinoma). Allocation concealment will be ensured by independence of the randomization service and release of the results after recruitment. Recruitment will be spread over 6 months with a subsequent 6-month intervention phase (Fig. 1).

**Fig. 1 Fig1:**
[figure not shown]
Study flow chart (IG: intervention group, CG: control group, V: visit)

### Objectives and endpoints

The objective of this interventional trial is to determine the effect of a continuously supervised post-surgery online training and lifestyle modification program on patients’ physical and psychological status. Short-term and intermediate-term aims are to increase the cardiopulmonary performance and muscle mass, to reduce abdominal fat, to improve the quality of life, and to reduce depression and fatigue. The recurrence rate and mortality will be addressed in the long term.

The primary endpoint is a 13% increase in the VO_2_ max in the IG when compared with the CG after training for 6 months.

Secondary endpoints after 6 months of online training and lifestyle improvement are as follows.
Significant decrease in re-hospitalization (decrease by absolute 15%) in the IG when compared with the CGSignificant improvement in the quality of life, fatigue, and depression (improvement in scores by absolute 10%) in the IG, which is assessed with the European Organization for Research and Treatment of Cancer Quality of Life Questionnaire (EORTC QoLQ-C30, disease specific adaptation)Increase in the metabolic rate by 500 kcal (500 Met/min) per week in the IG when compared with the CGIncrease in patients’ compliance to 95% in the IGImprovement/decrease in tumor-associated marker panel

### Sample size calculation

The sample size was calculated according to the expected effect on the primary endpoint (13% increase in VO_2_ max) in the IG when compared with the CG in 6 months [28, 29] for each cancer subgroup. Sample size calculation was based on a power of 0.80 with a two-sided test and an alpha of 0.05. The increase was calculated with respect to the change in the baseline characteristics of IG patients when compared with CG patients, with delta VO_2_ max of 3.6 ml/kg/min, a standard deviation of 5 ml/kg/min, and an average VO_2_ max of 27.5 ml/kg/min at baseline. Thus, the required sample size for each group (IG and CG) of each cancer entity (colorectal, breast, and prostate) was 40. Considering an expected dropout rate of 20%, 50 patients will be recruited (oversampling) for each group and entity. Considering 100 patients (50 in the IG and 50 in the CG) for each cancer entity, 300 patients will be included in the study.

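### The stated sample-size inputs give 31 to 32 evaluable patients per arm and entity, not 40; n = 40 and power 0.80 do not match, and the mismatch is conservative

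*Protocol article*

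**What the plan says.** All of the inputs stand in the Methods of the protocol article. Under Sample size calculation:

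- Error rates: "Sample size calculation was based on a power of 0.80 with a two-sided test and an alpha of 0.05".
- Effect: "delta VO_2_ max of 3.6 ml/kg/min".
- Variability: "a standard deviation of 5 ml/kg/min".
- Baseline level: "an average VO_2_ max of 27.5 ml/kg/min at baseline".
- Result, introduced as following from these inputs: "Thus, the required sample size for each group (IG and CG) of each cancer entity (colorectal, breast, and prostate) was 40".
- Dropout step: "Considering an expected dropout rate of 20%, 50 patients will be recruited (oversampling) for each group and entity".

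Randomization gives equal arms ("following a 1:1 allocation by the Clinical Trial Centre, Leipzig"). The Methods part of the abstract confirms that the overall figure already allows for losses: "total 300 patients including dropouts". The calculation is meant to hold separately within each of the three cancer entities, and the statistical analysis section likewise plans the analysis within the entity subgroups.

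**The concern.** The paragraph sets out a complete calculation for comparing two means and presents 40 per arm as its result. A reader who puts the printed inputs into the standard formula gets a clearly smaller number. The gap is 8 to 9 patients per arm, more than 20% of the stated figure, so rounding does not explain it.

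This paragraph is the only justification given for 300 patients. As printed, a reader cannot tell what each entity comparison was designed to do: whether the risk of missing the planned effect is about 11% or 20%, and whether alpha within an entity is really 0.05. Because the article prints both inputs and output, and they disagree, this is not a detail left to a fuller document.

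**Working it through.** **Inputs.** From Sample size calculation: difference 3.6, SD 5, two-sided alpha 0.05, power 0.80, dropout 20%. From Randomization: 1:1 allocation. The difference agrees with the 13% target: 0.13 × 27.5 = 3.575, or 3.6 rounded. The standardised effect is 3.6/5 = 0.72.

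**The plan's own chain after 40.** 40/(1 − 0.20) = 50 per arm; 2 × 50 = 100 per entity; 3 × 100 = 300. This part is arithmetically correct. The step that fails is the one leading to 40.

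**Required number per arm.**

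- Normal approximation: n = 2 × (1.960 + 0.8416)² × (5/3.6)² = 2 × 7.849 × 1.929 = 30.3, so 31.
- Two-sample t test (noncentral t): 31.3, so 32.
- With the unrounded difference of 3.575 the results are again 31 and 32.

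**Power at given sizes** (t test, two-sided 0.05):

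| Evaluable per arm | Power |
|---|---|
| 32 | 0.809 |
| 40 | 0.889 |
| 50 | 0.946 |

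The normal approximation at 40 gives 3.6/(5 × √(2/40)) − 1.960 = 3.220 − 1.960 = 1.260, hence 0.896. Conversely, 40 per arm at power 0.80 corresponds to a difference of 3.17 with SD 5, or to an SD of 5.68 with a difference of 3.6.

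**What could have produced 40.**

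| Explanation | Per arm (normal / t) | What it changes |
|---|---|---|
| Dropout applied twice | 32/0.8 = 40, then 40/0.8 = 50 | 40 would be a recruited number, not the required number |
| Power 0.90 | 41 / 42 | the stated power |
| Alpha 0.05/3 | 41 / 42 | the stated alpha; at 40 per arm, power would be 0.778 |
| SD 5 is that of single values, and change is compared | 40 at r ≈ 0.34 (normal) or r ≈ 0.36 (t test) | adds a correlation that is not stated |
| Rank test instead of t test | 33 to 37 | does not reach 40 |
| One-sided test | 24 / 25 | does not reach 40 |

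For the change-score row, SD(change) = 5 × √(2(1 − r)), where r is the assumed correlation between baseline and 6 months. The range is wide. By the normal approximation n is 61 at r = 0, 43 at r = 0.3, 39 at r = 0.36, 31 at r = 0.5 and 19 at r = 0.7.

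Adjusting for baseline instead of comparing change does not lead to 40 either. With residual SD 5 × √(1 − r²), n is 31 at r = 0 and falls from there (28 at r = 0.3, 23 at r = 0.5).

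**The case against.** The best defence concerns the SD. The paragraph refers to change, but does not say outright whether 5 ml/kg/min is the SD of change or of single VO2max values. If it is the latter and change scores are compared, a correlation of about 0.36 gives 40 per arm with every printed input intact; power at 40 would then be 0.80, not 0.89. This stands in part. It makes the figure of 0.89 conditional on 5 being the SD of the analysed outcome. It does not rescue the stated 40, because no correlation is given and the answer runs from 61 to 19 over assumed correlations of 0 to 0.7.

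A second objection is that nothing is harmed: the trial is larger than its inputs require, and an inconclusive entity result would be read from its confidence interval, which does not depend on the planned power. This is fair, and it bears on severity. It does not make the paragraph correct.

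A reader might also infer that dropout was certainly counted twice, and hence that 32/0.8 = 40 recruited per arm, 240 in total, would be enough and 60 patients are surplus. The document does not support that inference. It shows one dropout step, which is correct, and nowhere says that 40 already includes losses. The exact 32–40–50 chain is suggestive, but round numbers can coincide, and the other explanations come within one or two patients. Had 40 come from alpha 0.05/3, reducing to 32 would underpower the design. Moreover, the Trial status section says that recruitment began in August 2020, so a cut to 240 would be a design change, not a rewording.

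**Conclusion.** The sample-size paragraph does not reproduce. As a two-sample comparison with its printed inputs it requires 31 (normal) or 32 (t test) evaluable patients per arm and entity, against 40 stated. With 40 evaluable, power is about 0.89 by t test, so 40 and 0.80 do not match. This rests on reading 5 ml/kg/min as the SD of the analysed outcome, on equal arms, and on alpha 0.05 within each entity, as printed.

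It would be too strong to say that the trial misses its 80% power: on the stated inputs that target is exceeded. The cause of the mismatch cannot be settled from the article, and double dropout is only one of several candidates. The severity is that of a reporting correction that should be made; the endpoint and the planned analysis are unaffected.

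**What to change.** Keep 300 patients and correct the one paragraph:

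1. State which input or step produced 40.
2. State whether the SD of 5 ml/kg/min refers to change from baseline or to single values; if to single values, give the assumed correlation.
3. If the inputs stand as printed, restate the power, for example: with 40 evaluable patients per arm and entity, power is about 0.89 at two-sided alpha 0.05 for a difference of 3.6 ml/kg/min and an SD of 5 ml/kg/min.
4. Otherwise, print the alpha, power or SD actually used, so that inputs and result agree.

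The cost is a one-paragraph correction. No change in recruitment is needed.

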### Study organization

The central components of this new type of care are **c**ross-linked **c**are **p**oints (cCPs), which are located in the respective university hospitals. Their tasks include local project administration (patient recruitment, data collection) and medical health care supply (diagnostics, briefing, telemonitoring support, and cross-sectoral communication). Each cCP will consist of an interdisciplinary team (a physician, a sports scientist, and a cancer nurse). It will care for approximately 100 patients (50 patients each from the CG and the IG).

The medical duties within the cCP will include primary and follow-up care before and after the surgery and in-hospital rehabilitation immediately after the intervention period and 6 month after the intervention. The tasks will include data acquisition, medical supervision of the online program and training, management of patients’ information, structured tumor aftercare in accordance with the respective tumor guidelines, tele-support, and feedback to the referring ambulant physician. The responsibilities of sport scientists will include individual configuration of the intervention program (training and nutrition) and tele-support. The cancer nurses will perform the tasks of patient screening, management of patient information and patient inclusion, monitoring the online program, reporting of vital parameters and clinical chemistry, tele-support, data collection during and after the training, and central data management.

### Cross-sectoral patient file and CRBP-TS application

The organizational and information technology center of the project will include the **e**lectronic cross-**s**ectoral **p**atient file (ESP) and the CRBP-TS application. At baseline, the CRBP-TS mobile application will be downloaded in each participant’s tablet (Lenovo Tab M10 TB-X606X; Lenovo, Hongkong, China) and connected to the activity device (Vivoactive 4; Garmin, Olathe, Kansas, US) via Bluetooth. The activity device will be wear 24 h a day during the entire study period. The CRBP-TS application will be regularly used by the participant to transfer activity tracker and heart rate (chest belt) data via Bluetooth throughout the intervention, to complete questionnaires, and to visualize the home-based training in the intervention group. An automatic data transfer from patient to ESP is provided via an internet access (LTE, Deutsche Telekom AG, Germany) at the tablet divice. The ESP will serve as an electronically case report form (CRF) and will contain the medical report files, patients’ training data, measurements, and manual entries. The data will be prepared and provided to the participating care institutions. Patients will also be able to view their training, fitness, and body composition data.

### Data management and statistical analysis

In the CRBP-TS study, all data will be entered to the ESP at the participating site. All questionnaires will be completed on a dedicated application CRBP-TS and merge to the ESP. There will not be a formal data monitoring committee for this study, however monitoring will be provided by the trail administration stuff, including overall project supervision and progress monitoring. The clinical research assistant will verify all consent forms, compliance with established protocol and procedures, and data quality in the ESP. Following quality control measures, the input data will be locked in the database. Participant files will be maintained in the storage for a period of 10 years after the completion of the study. The access to the ESP will be secured (personal ID and password required) with different levels of security depending on the role of the investigator. The Principal Investigator will be given access to the cleaned data sets.

The evaluation will be performed by an “intent to treat” analysis using all randomized patients in the entity subgroups. For the evaluation, established statistical programs and common statistical analysis methods for longitudinal regression models (such as mixed model with repeated measures) will be used. The intervention arm will be compared with the control arm with respect to all primary analyses and all visits.

### Individual study plan, measurements, and data collection

A period of 6 months is planned for the recruitment of participants. The intervention period will be of 6 months. Data collection will be performed at baseline (appointment 1a will include examinations and appointment 1b will include instruction course), at 3 months (appointment 2), and at 6 months (appointment 3, end of the study). After 12 months, a follow-up investigation (appointment 4) will be conducted. The IG will undergo individual training intervention and counseling, while patients from the CG will be provided with standard care as well as comprehensive information regarding health-promoting measures. The daily activity of patients in the IG and the CG will be measured and evaluated by the CRBP-TS application. An overview of the examinations during the study visits is shown in Fig. 2.

